**Fig. 1 Fig1:**
[figure not shown]
Study workflow

**Table 1 Tab1:** Study design, timing of pre- and postoperative use of RxWell™, and follow-up evaluations

Outcomes	Instrument	Study period	*Eligibility assessment*	*Enrollment*	*Surgery*	*Post-Surgery*		
		*Time*	*After consenting the patient*	*Baseline (3–4 weeks before surgery)*		*1M*	*2M*	*3M*
*Primary outcomes*								
Self-reported anxiety	*PROMIS 4a anxiety*		x	x	x	X	x	x
	*GAD-7*			x^a^	x^a^	x^a^	x^a^	x^a^
Self-reported depression	*PROMIS 4a depression*		x	x	x	x	x	x
	*PHQ-8*			x^a^	x^a^	x^a^	x^a^	x^a^
*Secondary outcomes*								
Sleep disturbances, fatigue, ability to participate in social roles	*PROMIS 29+2 (Except PROMIS 4a Anxiety and 4a Depression)*			x	x	x	x	x
Pain catastrophizing	*Pain Catastrophizing Scale*			x	x	x	x	x
Perioperative pain	*Pain Scores*			x	x	x	x	x
Opioid and non-opioid consumption				x	x	x	x	x
Functionality	*HOOS/KOOS*			x	x	x	x	x
Post-surgical complications						x	x	x
Patient satisfaction								x

^a^The intervention group will also be assessed bi-weekly with GAD-7 and PHQ-8 through the RxWell app

**Table 2 Tab2:** CONSORT 2010 items and CONSORT-SPI 2018 checklist for the abstract

Section	CONSORT abstract item	Relevant CONSORT-SPI item	Reported on page #
Title	Identification of the study as randomized		1
Authors	Contact details for the corresponding author		1–2
Trial design	Description of the trial design (e.g., parallel, cluster, noninferiority)	If the unit of random assignment is not the individual, refer to CONSORT for Cluster Randomized Trials and report the items included in its extension for abstracts	3
Methods			
Participants	Eligibility criteria for participants and the settings where the data were collected	When applicable, the eligibility criteria for the setting of the intervention delivery and the eligibility criteria for the persons who delivered the interventions	3
Interventions	Interventions intended for each group		3
Objective	Specific objective or hypothesis	If pre-specified, how the intervention was hypothesized to work	3
Outcomes	Clearly defined primary outcome for this report		3
Randomization	How participants were allocated to interventions		3
Awareness of assignment	Who was aware of intervention assignment after allocation (for example, participants, providers, those assessing outcomes), and how any masking was done		3
Results			
Number randomly assigned	Number randomized to each group		3
Recruitment	Trial status		3–4
Interventions		Extent to which interventions were actually delivered by providers and taken up by participants as planned	3–4
Number analyzed	Number analyzed in each group		N/A
Outcomes	For the primary outcome, a result for each group and the estimated effect size and its precision		N/A
Harms	Important adverse events or side effects		N/A
Conclusions	General interpretation of the results		N/A
Trial registration	Registration number and name of trial register		4
Funding	Source of funding		4

**Table 3 Tab3:** CONSORT 2010 items and CONSORT-SPI 2018 checklist for the main text

**Section**	**Item #**	**CONSORT-SPI 2010**	**CONSORT-SPI 2018**	**Reported on page #**
**Title and abstract**				
	1a	Identification as a randomized trial in the title^§^		1
	1b	Structured summary of trial design, methods, results, and conclusions (for specific guidance see CONSORT for Abstracts)^§^	Refer to CONSORT extension for social and psychological intervention trial abstracts	2
**Introduction**				
Background and objectives	2a	Scientific background and explanation of rationale ^§^		6-8
	2b	Specific objectives or hypotheses ^§^	If pre-specified, how the intervention was hypothesized to work	6-8
**Methods**				
Trial design	3a	Describe of trial design (such as parallel, factorial), including allocation ratio ^§^	If the unit of random assignment is not the individual, please refer to CONSORT for Cluster Randomized Trials	9
	3b	Important changes to methods after trial commencement (such as eligibility criteria), with reasons		N/A
Participants	4a	Eligibility criteria for participants^§^	When applicable, eligibility criteria for settings and those delivering the interventions	10
	4b	Settings and locations where the data were collected		10
Interventions	5	The interventions for each group with sufficient details to allow replication, including how and when they are actually administered ^§^		16-17
	5a		Extent to which interventions were actually delivered by providers and taken up by participants as planned	N/A
	5b		Where other informational materials about delivering the intervention can be accessed	
	5c		When applicable, how intervention providers were assigned to each group	
Outcomes	6a	Completely defined pre-specified outcomes, including how and when they were assessed^§^		12-15
	6b	Any changes to trial outcomes after the trial commenced, with reasons		N/A
Sample size	7a	How sample size was determined^§^		11-12
	7b	When applicable, explanation of any interim analyses and stopping guidelines		N/A

**Results**				
Participant flow (a diagram is strongly recommended)	13a	For each group, the numbers randomly assigned, receiving the intended intervention, and analyzed for the outcomes^§^	Where possible, the number approached, screened, and eligible prior to random assignment, with reasons for non-enrolment	Fig 1
	13b	For each group, losses and exclusions after randomization, together with reasons^§^		22
Recruitment	14a	Dates defining the periods of recruitment and follow-up		N/A
	14b	Why the trial ended or was stopped		N/A
Baseline data	15	A table showing baseline characteristics for each group^§^	Include socioeconomic variables where applicable	N/A
Numbers analyzed	16	For each group, number included in each analysis and whether the analysis was by original assigned groups^§^		N/A
Outcomes and estimation	17a	For each outcome, results for each group, and the estimated effect size and its precision (such as 95% confidence interval)^§^	Indicate availability of trial data	N/A
	17b	For binary outcomes, the presentation of both absolute and relative effect sizes is recommended		N/A
Ancillary analyses	18	Results of any other analyses performed, including subgroup analyses, adjusted analyses, and process evaluations, distinguishing pre-specified from exploratory		N/A
Harms	19	All important harms or unintended effects in each group (for specific guidance see CONSORT for Harms)		N/A
**Discussion**				
Limitations	20	Summarize the main results (including an overview of concepts, themes, and types of evidence available), link to the review questions and objectives, and consider the relevance to key groups.	Trial limitations, addressing sources of potential bias, imprecision, and, if relevant, multiplicity of analyses	N/A
Generalizability	21	Discuss the limitations of the scoping review process.	Generalizability (external validity, applicability) of the trial findings^§^	N/A
Interpretation	22	Provide a general interpretation of the results with respect to the review questions and objectives, as well as potential implications and/or next steps.	Interpretation consistent with results, balancing benefits and harms, and considering other relevant evidence	N/A
**Important information**				
Registration	23	Registration number and name of trial registry		21
Protocol	24	Where the full trial protocol can be accessed, if available		21
Declaration of Interests	25	Sources of funding and other support; role of funders	Declaration of any other potential interests	21
Stakeholder investments	26a		Any involvement of the intervention developer in the design, conduct, analysis, or reporting of the trial	N/A
	26b		Other stakeholder involvement in trial design, conduct, or analyses	N/A
	26c		Incentives offered as part of the trial	N/A

All patients will be assessed either in person at the initial visit or via telemedicine technologies (text or video) at baseline, on the day of surgery, and 1, 2, and 3 months after the surgery. We will evaluate how patients comply with and respond to RxWell together with weekly supports. We will then determine the program's efficacy in ameliorating symptoms.

### Study participants

#### Sampling method

The target population is patients undergoing elective primary total hip or primary total knee replacements at UPMC (Shadyside, Magee, Passavant, and East) and are found to have high levels of anxiety and/or depression using validated surveys. We will use the Patient-Reported Outcomes Measurement Information System (PROMIS) scales for the assessment of anxiety and depression. The sampling method will be a convenience sampling.

##### Inclusion criteria

Eligible participants will be adult patients undergoing primary total hip or knee arthroplasty for a degenerative condition, who can read and speak English, with access to a smart phone or tablet and with a T-score ≥ 60 in short PROMIS Anxiety and/or Depression short forms 4a.

##### Exclusion criteria

Patients will be excluded from the study if they meet any of the following criteria: plans to undergo a non-elective surgery or secondary arthroplasty; profound mood disorder that requires emergent care, defined as a *T*-score > 70 in PROMIS Anxiety 4a and/or Depression 4a forms, neurocognitive impairment, dementia or active delirium, or severe intellectual disability; and no access to a smartphone or tablet.

#### Sample size calculation

This is a pilot study meant to inform a subsequent RCT based on this treatment. We will determine if the study is a success if this effect size is observed in our primary outcomes and thus our study is powered based on these effects. From observed estimates in concurrent studies, we expect a clinically significant effect size of Cohen’s D greater than or equal to 0.8. Our primary analysis is comparing PROMIS T scores, GAD-7 and PHQ-8 between groups on day of surgery. Therefore, with 95% confidence, 80% power, using two sided tests and assuming a 50% retention rate, our desired sample size is 136. We will utilize 1:3 allocation, randomizing 34 to the control group and 102 to the intervention group. We are allocating 1:3 to get more accurate estimates around within treatment group improvements as well as to increase the number of patients we can potentially aid by supplying them with the low-risk treatment. The 1:3 allocation was chosen based on the study design and the nature of the intervention. This is a proof-of-concept study in which we want to evaluate the feasibility of RxWell™. In addition, our target subjects are patients with a moderate level of anxiety and/or depression, and we consider it is more ethical to offer a treatment to as many subjects as possible. Sample size calculations were conducted using the Power Analysis and Sample Size Software (PASS - 2022). NCSS, LLC. Kaysville, Utah, USA.

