## Materials and methods

### Study design

This is a prospective, randomized, controlled clinical trial in a multi-hospital health care system among patients with high levels of anxiety with an indication for primary total hip or knee arthroplasty. We will be comparing two groups: one that receives access to RxWell™ and usual care and one that only receives the usual care. Figure 1 and Table 1 show the study design, timing of pre- and postoperative use of RxWell™, and follow-up evaluations. CONSORT 2010 items and CONSORT-SPI 2018 checklist are presented for the abstract (Table 2) and main text (Table 3). The SPIRIT Checklist is presented as an additional file (Additional file 1). We will recruit patients from 4 hospitals within the *UPMC system* (*UPMC Shadyside*, *Magee*, *East*, and *Passavant hospitals*). In this pilot, randomized feasibility trial, we will prospectively allocate 34 subjects in the control group, and using a 1:3 allocation, we will have 102 in the intervention group (two-sided *t*-test with alpha of .05, power of .8, with a 3:1 ratio and a 50% drop out rate for a Cohen’s *d* of .8). A block randomization schedule generated using the R software (version 4.2.1, R Core Team, 2022) will be used to allocate the participants to either dCBI plus usual care (*intervention*) or usual care (*control*) with a 3:1 allocation (Table 2). Investigators will be blinded for group assignment in REDCap, and they will also be blinded for the monthly reports. Research coordinators, the statistical data analysts, and subjects will not be blinded. To make sure investigators are blinded to the intervention, investigators will not have access to the randomization table and surveys in REDCap. Investigators will only be able to access the eligibility checklist and informed consent surveys in REDCap. Patients will be randomized immediately after the PROMIS Anxiety 4a and the PROMIS Depression 4a patient assessment by a research coordinator using REDCap. We do not anticipate any requirement for unblinding, but if required, the director of clinical research operations, regulatory specialist, study coordinators, or the principal investigator will have access to group allocations and any unblinding will be reported.

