### Data analysis

The primary hypotheses and all other comparisons will be assessed with intention to treat estimates. Between-group differences in primary outcomes, PROMIS anxiety and depression scores, PHQ-8, and GAD-7 scores will be tested using independent two sample *t*-tests on the day of the surgery. Two-sided tests using *p* values of < 0.05 will be considered statistically significant. Differences of tests showing Cohen’s *D* of > = 0.8 will be considered clinically significant. Participants with missing primary timepoint data will be excluded from testing. For secondary outcomes, we will calculate descriptive statistics i.e., usage of RxWell™, adherence, use frequency, etc. Testing of treatment and control group differences in secondary outcomes will be applied to appropriate variables, i.e., participant perioperative pain, opioid equivalent requirement, functional recovery, etc., for time point baseline, day of surgery, and 1 month follow-up. Continuous variables will be described using means and standard deviations. Categorical variables will be described using frequencies/proportions. We will use independent sample *t*-tests and chi-squared analyses to examine between group differences. Fisher’s exact tests and Mann-Whitney *U* tests will be performed in replacement of their counterpart parametric tests where appropriate. Missing data will be removed from denominators, proportions, distributions, and testing of their differences. We will use longitudinal mixed effect models to account for within person variance across all time points as a secondary analysis.

Baseline patient demographics, comorbidities, and procedure details will be stratified by group, and described standardized mean differences will be calculated to compare groups (Table 1). As a secondary analysis, we will use longitudinal mixed effect models to account for within person variance across all time points. We will adjust models using demographics found to have greater than 0.2 standardized mean difference. No subgroup analysis will take place.

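### The stated 80% power does not belong to the stated success rule: at a true Cohen's d of 0.8, an observed d of at least 0.8 occurs only about half the time per scale

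*Protocol article*

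**What the plan says.** Three statements in the protocol article bear on this.

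- **Success rule.** The Sample size calculation section states "We will determine if the study is a success if this effect size is observed in our primary outcomes". It links this to the power with a consequential clause, and the next sentence names the effect size: "we expect a clinically significant effect size of Cohen’s D greater than or equal to 0.8".
- **Power.** The same section gives "with 95% confidence, 80% power, using two sided tests and assuming a 50% retention rate, our desired sample size is 136" and "We will utilize 1:3 allocation, randomizing 34 to the control group and 102 to the intervention group". The Study design section shows what the 80% refers to: a two-sided t-test "with alpha of .05, power of .8", for a Cohen's d of 0.8 with 50% dropout.
- **Analysis.** The Data analysis section keeps two labels. For the t-tests, p "values of < 0.05 will be considered statistically significant"; separately, a Cohen's d "of > = 0.8 will be considered clinically significant". Participants without day-of-surgery data are left out of the test.

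The primary comparison covers four scores on the day of surgery: PROMIS anxiety, PROMIS depression, GAD-7 and PHQ-8. The success sentence does not say whether one, some or all of them must reach the threshold.

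**The concern.** The value 0.8 does two jobs. It is the true effect assumed for the power calculation, and it is the threshold that the observed effect must reach for success. An estimate is roughly centred on its true value. If the truth equals the threshold, the estimate clears it about half the time, whatever the sample size. The 80% describes a different and easier event, p < 0.05.

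A reader who takes the section at its word will think that a programme with the planned effect has an 80% chance of being called a success. The protocol says the pilot is meant to inform a later RCT, so how its success is read matters. A result with an observed d between about 0.56 and 0.80 would be statistically significant and still miss the success rule.

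**Working it through.** **Inputs.** d = 0.8, two-sided alpha 0.05, 80% power, 1:3 allocation, 34 and 102 randomised, 50% retention (Study design; Sample size calculation). Completers are therefore 34 × 0.5 = 17 and 102 × 0.5 = 51.

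**1. The plan's own figure.** By the normal approximation, control n = (1.960 + 0.842)² × (1 + 1/3) / 0.8² = 16.4, rounded up to 17. With 51 in the intervention group that makes 68, and 68 / 0.5 = 136. The plan's 136 reproduces.

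**2. Power for p < 0.05.** Let c = √(n₁n₂/(n₁+n₂)) = √(17 × 51 / 68) = 3.571, so the approximate standard error of d is 1/c = 0.280. The noncentral t with 66 df and noncentrality 0.8 × 3.571 = 2.857, against a critical t of 1.997, gives power 80.4%. The smallest significant observed d is 1.997 / 3.571 = 0.559.

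**3. Chance of meeting the success rule on one scale.** The observed d is t/c, so P(observed d ≥ 0.8) is the probability that a noncentral t (df n₁+n₂−2, noncentrality true d × c) is at least 0.8 × c.

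| True d | 17 vs 51 | 34 vs 102 |
|---|---|---|
| 0.5 | 15% | 7% |
| 0.8 | 50.4% | 50.3% |
| 0.9 | 64% | 69% |
| 1.0 | 76% | 84% |
| 1.2 | 92% | 98% |

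With a small-sample (Hedges) correction to d, the 50.4% becomes 49.2%. An 80% chance needs a true d of about 1.04 at 17 vs 51, or 0.97 at 34 vs 102.

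**4. The gap between the two rules at a true d of 0.8.** At 17 vs 51, 80.4% − 50.4% = 30% of trials would be significant on a given scale and still miss the threshold. With full retention, power for p < 0.05 rises to 98.0% but the success probability stays at 50.3%, so the gap widens to about 48%. More patients do not repair the rule.

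**5. Four scales.** The documents give no correlations between the scales, so I assumed a common value and simulated 17 vs 51 with a true d of 0.8 on every scale.

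| Assumed correlation | All four d ≥ 0.8 | At least one d ≥ 0.8 |
|---|---|---|
| 0.3 | 14% | 87% |
| 0.5 | 20% | 81% |
| 0.7 | 27% | 74% |
| 0.8 | 32% | 70% |

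**6. Would p < 0.05 alone restore the 80%?** Only on a single scale. In the same simulation, p < 0.05 on all four scales has probability of about 50% to 71% (correlation 0.3 to 0.9). If any one scale suffices without adjustment, the chance of at least one false positive under no effect is about 10% to 17% over the same range.

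**The case against.** The strongest points on the other side are these.

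- **The power calculation is right.** The study is powered at d = 0.8, 136 reproduces, and the Study design section ties the 80% openly to a t-test. Nowhere does the protocol state an 80% chance of observing d ≥ 0.8. This stands. A reader might infer that the sample size is wrong or the trial too small, but the documents do not support that. The fault is that the success criterion and the powered test differ while the text presents one as following from the other.
- **The plan expects 0.8 or more, not exactly 0.8.** This also stands: one-half is the figure at the lower edge of that expectation, and it rises to 76% at a true d of 1.0. But 0.8 is the value used for the power, so it is the fair point of comparison.
- **One-half is neither floor nor ceiling over four scales.** Correct. A reader might assume that all four must pass and quote only the low figures. The text does not say so, and accepting any one scale gives well over half.
- **Nothing hangs on the rule.** A reader might take it as a go/no-go gate that discards the treatment. No section makes the larger trial conditional on it: the Long-term follow-up section already speaks of a larger trial with a waitlist design, and the Data analysis section sets separate feasibility targets. That consequence should not be claimed.
- **A demanding threshold suits a proof of concept.** With no true effect, one scale reaches d ≥ 0.8 in only about 0.3% of trials (17 vs 51). Keeping the rule is defensible, provided its success probability is stated.

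**Conclusion.** The point holds in a limited form, as a should-fix. The protocol defines success by an observed d of at least 0.8 and attaches to it a power that belongs to p < 0.05. At the true effect used for planning, the success rule is met about 50% of the time per scale instead of 80%, and enlarging the trial does not change that. The single-scale figures rest on the protocol's own inputs and on the usual t-test model of normal outcomes with equal variances.

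Over the four scales, the chance at that same true effect lies anywhere from about 14% to 87%, depending on a combination rule that the success sentence leaves open. Those figures also assume the same true d on every scale and a common correlation of 0.3 to 0.8. The sample size, the test and the data collection are unaffected.

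**What to change.** Choose one of two repairs before results are known.

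**(a) Align success with the powered test.** Define success as p < 0.05 on the day of surgery, either on one named primary scale, for which the 80% is correct, or under a stated rule for combining the four. If any one scale suffices, adjust for multiplicity; if all must pass, restate the power. Report the difference and d with 95% confidence intervals, and keep d ≥ 0.8 only as a descriptive benchmark of clinical relevance.

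**(b) Keep the observed-d rule.** State how the four scales combine. Give the rule's own success probability, about 50% per scale at a true d of 0.8, in place of the 80%, and describe the 80% only as power for p < 0.05.

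Either way the change is wording in the Sample size calculation and Data analysis sections. No extra patients are needed. The cost is a less favourable stated chance of success under (b), or under (a) if all four scales must pass.

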### Outcome measures

We will assess the following:RxWell™’s acceptance by practitioners and patients will be measured by qualitative interviews among all practitioners and randomly selected patients.Workflow changes brought on by the implementation of RxWell™, andImpact of RxWell™, on mood disorders (anxiety, depression, pain catastrophizing) in the immediate pre- and post-operative periods.

We will also test the impact of RxWell™, onSleep disordersFatigueAbility to participate in social rolesPain interferenceCognitive functionPerioperative painOpioid requirements and opioid morphine equivalents,Functional recovery, andResource utilization associated with the surgery and recovery (hospital length of stay, duration of physical therapy).

Ultimately, our outcome is to determine if RxWell™ can improve surgical outcomes.

Primary and secondary outcomes will be measured at baseline preoperatively, on the day of the surgery, and 1, 2, and 3 months after surgery (Table 1). Preoperative data will be collected virtually via REDCap surveys by study team members. Postoperative data collection will be performed via email surveys and telephone calls by a member of the study team. Research coordinators collecting outcomes will not be blinded to group assignment. Patients will not be blinded and will be informed that the study aims to assess the effect of dCBI in addition to usual care compared to usual care alone on surgical patients.

